### Study Setting and Staff

The PHSKC SHC provides direct medical services related to sexual health and STI to over 6500 patients each year and is the largest single diagnosing site for HIV infection in the Pacific Northwest region of the US. Of all patients seen annually in the SHC, approximately 41% identify as sexual minority men and 42% as racial or ethnic minorities. Disease and research intervention specialists (DRIS), who are nonclinical public health staff trained in HIV and STI prevention and to provide partner services, currently serve as PrEP navigators and conduct all PrEP initiation and nonclinical monitoring visits in the SHC [32]. They will continue to fulfill this role during the study, augmenting their current work to manage HB-PrEP, and along with the lead research coordinator will help with eligibility screening, recruitment, and retention efforts.

### Primary RCT

#### Eligibility Criteria and Exclusions

All patients in the SHC meet both PrEP use criteria according to the US Centers for Disease Control and Prevention’s 2021 clinical practice guidelines [12] and at least one of three PHSKC PrEP criteria: (1) HIV-negative cisgender man, transgender or nonbinary person who has sex with men; (2) person who has a sex partner with unsuppressed HIV; or (3) person who injects drugs or engages in exchange sex [32]. Prospective participants for the trial, in addition, must meet the following study-specific criteria (Textbox 2).

Persons with active hepatitis B or a creatinine clearance <50 mL/minute are not excluded; however, they will receive counseling about the risk of hepatitis B infection worsening if PrEP medications are discontinued and be encouraged to follow up with medical providers outside of the study for management of comorbid conditions.

Inclusion and exclusion criteria.
**Inclusion criteria**
Age ≥18 years.Resident of Washington State.Can speak, understand, read and write in English or Spanish.Current pre-exposure prophylaxis user or interested in starting or restarting pre-exposure prophylaxis.Willingness to be randomized to home-based pre-exposure prophylaxis and adhere to specified procedures.Willingness to provide primary and alternate contact information.
**Exclusion criteria**
Recent (<4 weeks) “high risk” HIV exposure while off pre-exposure prophylaxis or symptoms of acute HIV infection.No mailing address to receive packages or sampling kits.No stable, working telephone number.No smartphone or electronic device with internet access.History of bleeding disorder, current or recent (≤7 days) use of anticoagulant medications (warfarin and rivaroxaban).Pregnancy.

#### Screening, Recruitment, and Enrollment

##### Existing Patients

DRIS or the research staff review patients scheduled for routine PrEP visits at the SHC and offer enrollment in person to eligible patients. Enrollees are randomized to continue SOC (attend the PHSKC SHC every 4 months for a visit with DRIS, have blood samples collected for PrEP monitoring, and perform self-collection of GC and CT swabs) or have the option to do HB-PrEP monitoring. Those assigned to HB-PrEP (intervention arm) are eligible to participate in home-based monitoring immediately after receiving instruction from study staff on how to use the Tasso devices, procedures for mailing kits back to the PHSKC laboratory, and how to complete web-based surveys after returning kits. DRIS or research staff facilitate training on the use of the Tasso devices. This includes a review of the test kit components, the importance of warming the upper arm, aseptic technique, and proper use of the device. After the overview, participants were also asked to watch the training video provided by Tasso (Tasso Inc) [30].

##### New and Former (“Lost to Follow-Up”) PHSKC PrEP Patients

Prospective and former PrEP patients who are eligible for the study may be recruited at their initial visit. Those randomized to the control arm will adhere to the usual SHC PrEP clinical protocols [32]. Persons randomized to HB-PrEP receive instruction from DRIS or study staff about self-collection procedures as above and are eligible to return their first kit for the month 4 monitoring cycle. Persons initiating PrEP (or reinitiating after a prolonged discontinuation) must be evaluated in person by a clinician and have blood collected by clinic staff for HIV screening, renal function, viral hepatitis serologies, and so on; thus, these individuals will become eligible to use home kits at their first tri-annual follow-up (ie, 120 days after PrEP initiation). Follow-up time in the study for all participants begins immediately after enrollment.

#### Randomization and Study Procedures

##### Sample Size and Power Considerations

Sample size calculations for the primary Kaplan-Meier survival analysis were based on standard methods [33]. Assuming that 2.5% of individuals discontinue PrEP per month in the control arm, we expect 45% of SOC participants to discontinue PrEP (55% retention) over the 20-month study period. In the intervention arm, we estimate that 70% will adopt HB-PrEP. We assume a relative risk of discontinuation of 0.6 among participants assigned to receive HB-PrEP leading to a 32% discontinuation rate (68% retention) in the HB-PrEP arm. We also allowed for an overall dropout rate in both groups of 6% [15]. Thus, a sample size of 458 participants should yield 80% power to detect a 13% point difference in PrEP retention. All eligible participants are assigned through simple 1:1 randomization to either the intervention arm (n=229) or SOC arm (n=229) and followed for 20 months. RCT procedures are detailed in Textbox 1.

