Structural barriers such as lack of access to PrEP medical providers and the burden of quarterly clinical monitoring visits have stymied PrEP scale-up in the United States for years [7-9]. PrEP retention (defined as maintaining all aspects of PrEP care, including attending follow-up visits and obtaining monitoring tests every 3 months according to US guidelines [10]) represents a substantial gap in the PrEP care continuum [11,12]. Studies on national PrEP retention rates suggest only 56% of individuals who initiate PrEP remain on PrEP for at least 1 year, and only 41% persist through year 2 [13]. Younger age, Black race, and unstable or lower income are each associated with discontinuations and being lost to follow-up [14]. We have observed similar levels of PrEP retention in the PHSKC Sexual Health Clinic (SHC), with 40% of PrEP users discontinuing the intervention at least once within 12 months [15]. The COVID-19 pandemic created dramatic reductions in sexual health service capacity [16] that only further exacerbated and continues to impact existing structural barriers that lead to lower PrEP access and higher numbers of discontinuations [17-19]. Among sexual minority men newly diagnosed with HIV in King County, previous PrEP use and discontinuations are common and underscore the urgent need to develop and implement novel targeted strategies to minimize barriers and provide individuals with more options to stay on PrEP [20].

Home-based PrEP (HB-PrEP), whereby an individual self-collects PrEP monitoring specimens at home, mails them into a laboratory for testing, and follows up with a provider remotely to renew PrEP prescriptions, has the potential to decrease PrEP access barriers and increase PrEP continuation rates. Studies confirm that patients are comfortable self-collecting bacterial sexually transmitted infection (STI) screening specimens [21] and that HB-PrEP monitoring is acceptable and often preferable to in-person care [11,22,23]. Configuring PrEP programs to users’ needs can optimize both uptake and delivery [24]. Particularly for young sexual minority men, programs that are convenient, discreet, and provide them with agency over PrEP use and monitoring may reduce the stigma associated with PrEP use, and increase PrEP uptake and retention [11,23]. Furthermore, HB-PrEP may decongest high-volume clinical sites and create additional capacity to grow PrEP programs.

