#### Outcomes and Analyses

##### Primary Outcome Measures

Effectiveness will be evaluated with a survival analysis using PrEP nonretention as the event of interest. Observation time for all participants begins at the time of randomization and continues until either loss-to-follow-up or study end at 20 months. Consistent with previous studies [36,37], we define participants in either arm as “retained” on PrEP if they complete monitoring tests and visits with a clinician or DRIS at each 4-month interval to receive a renewed PrEP prescription. Kaplan-Meier curves will compare PrEP retention rates between the intervention and control arms at 20 months. We will use Cox proportional-hazards regression models to examine individual-level correlates (age, race and ethnicity, income range, and education status) of PrEP retention.

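### A 2.5% monthly rate, a 20-month horizon and 45% control discontinuation cannot all hold; the 80% power follows from the 45%, and would be about 69% if 2.5% is the intended input

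*Protocol article*

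**What the plan says.** Under Sample Size and Power Considerations, the control arm is described in two ways in one sentence, a monthly rate and a cumulative risk presented as its consequence: "Assuming that 2.5% of individuals discontinue PrEP per month in the control arm, we expect 45% of SOC participants to discontinue PrEP". The same sentence ties the cumulative risk to the study's length: "we expect 45% of SOC participants to discontinue PrEP (55% retention) over the 20-month study period".

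For the intervention arm the section says "In the intervention arm, we estimate that 70% will adopt HB-PrEP" and "We assume a relative risk of discontinuation of 0.6 among participants assigned to receive HB-PrEP", and arrives at 32% discontinuation (68% retention). It allows separately for 6% dropout in both groups and concludes: "Thus, a sample size of 458 participants should yield 80% power to detect a 13% point difference in PrEP retention". Allocation is 1:1, 229 per arm. Neither alpha nor sidedness is given.

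Primary Outcome Measures confirms the horizon: "Observation time for all participants begins at the time of randomization and continues until either loss-to-follow-up or study end at 20 months".

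**The concern.** The 45% is offered as what the monthly rate produces over the study, but a constant 2.5% per month over 20 months produces a lower figure. The error is not confined to that sentence. The 32% in the intervention arm is derived from the 45%, and the 13-point target, the 80% power and N = 458 follow from the pair.

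A reader cannot tell which control rate the trial was planned on. If it was 2.5% per month, the risk of missing an effect of the planned relative size is about 31% rather than the 20% implied, and a null result on the primary outcome would be read against a power claim that the stated rate does not support.

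**Working it through.** **Inputs.** From Sample Size and Power Considerations: control rate 2.5% per month; control risk 45%; adoption 70%; relative risk 0.6; intervention risk 32%; dropout 6%; 229 per arm. From Primary Outcome Measures: 20 months. Assumed: two-sided 5%. It is the choice that reproduces 458; one-sided 5% needs only about 335 to 345 before dropout.

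**Step 1: the intervention figure.** Applying 0.6 to the 70% who adopt and 1 to the rest gives 0.7 × 0.6 + 0.3 = 0.72 overall. Then 0.45 × 0.72 = 32.4%, stated as 32%. Applying 0.6 to everyone assigned would give 0.45 × 0.6 = 27%, which is not the stated figure. So 0.72 is the reading the document's own arithmetic supports, although its wording attaches 0.6 to all assigned.

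**Step 2: reproduce the stated design (45% versus 32%).**
- Evaluable: 458 × 0.94 = 430.5, about 215 per arm.
- Log-rank (Schoenfeld): HR = ln(0.68)/ln(0.55) = 0.645. Expected events = 430.5 × (0.45 + 0.32)/2 = 165.8. Power = Φ(½√165.8 × |ln 0.645| − 1.96) = 0.81.
- Two proportions: 0.13/√[(0.45 × 0.55 + 0.32 × 0.68)/215] − 1.96 = 0.83, giving power 0.80.
- Required N by Schoenfeld: 164 events, 426 participants, 426/0.94 = 453. Freedman gives 467 and two proportions 466. All are close to 458.

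The step from 45% versus 32% to N and power is therefore sound. (With the unrounded 32.4%, Schoenfeld power at N = 458 is 78%.)

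**Step 3: from the monthly rate to the 20-month risk.**

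| Conversion of 2.5% per month over 20 months | Result |
|---|---|
| Monthly compounding, 1 − 0.975^20 | 39.7% |
| Constant hazard, 1 − exp(−0.025 × 20) | 39.3% |
| Simple sum, 20 × 2.5% | 50% |
| Stated | 45% |

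In the other direction, 45% at 20 months needs 1 − 0.55^(1/20) = 2.94% per month by compounding, or −ln(0.55)/20 = 2.99% as a hazard.

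**Step 4: carry 2.5% per month through, everything else unchanged.**
- Compounding: control 39.7%; intervention 0.3973 × 0.72 = 28.6%; retention 60.3% versus 71.4%; difference 11.1 points.
- Constant hazard: 39.3% versus 28.3%; difference 11.0 points.
- Log-rank for the compounded figures: HR = ln(0.714)/ln(0.603) = 0.665; 430.5 × (0.397 + 0.286)/2 = 147 events; power 0.69 to 0.70. Constant-hazard figures give 0.69.
- Two proportions: 0.111/√[(0.603 × 0.397 + 0.714 × 0.286)/215] − 1.96 = 0.49, giving 0.69.
- Across formulas, and with or without the 6% dropout, power runs from 68% to 72%.
- For 80% power with 6% dropout, about 590 to 616 participants would be needed.
- At N = 458 and about 60% control retention, 80% power is reached only at about 12.6 points: 0.126/√[(0.603 × 0.397 + 0.729 × 0.271)/215] = 2.80 = 1.96 + 0.84.

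**The case against.** The strongest reply is that 45% is itself a stated input, and the one the calculation uses. If 2.5% is the slip and about 2.9% to 3.0% was meant, the 80% is right and nothing downstream changes. This stands. It rules out saying flatly that the trial has 69% power; that figure is conditional on 2.5% being intended.

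Two stronger readings are tempting and should not be adopted.

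- *A reader might infer that 45% is a 24-month figure carried into a 20-month study.* The match is close (1 − 0.975^24 = 45.5%; constant hazard 45.1%), but the document never says so. Other routes reach the same number: 18 × 2.5% = 45%, and 39.3% plus the 6% dropout is 45.3%, although dropout is listed as a separate allowance. The origin cannot be settled from the text.
- *A reader might set the rate against the clinic's own experience in the Background,* "with 40% of PrEP users discontinuing the intervention at least once within 12 months". That is a different measure (any discontinuation at least once, not retention at each 4-month interval) and perhaps a different population: among early enrollees with data, 89% were already taking PrEP. Extending it to 20 months also needs a constant hazard. It shows no contradiction.

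It can also be said that the 69% depends on how the inputs are read, and this is partly right. Simple summation gives 50% versus 36%, 14 points and about 84% to 85% power, but it is not the usual reading for a survival analysis and also misses 45%. Taking 0.6 for everyone assigned gives about 16 points and about 95% power, but does not yield the stated 32%. Taking 0.6 as a hazard ratio among adopters gives about 9 points and 52% to 57%. These alternatives are reasons to state the assumptions; none of them makes 2.5%, 20 months and 45% agree.

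Finally, a planning mismatch does not bias the treatment comparison. True, but it affects how a null result should be read.

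**Conclusion.** The point holds as an internal contradiction: the monthly rate, the horizon and the 45% cannot all be right. The gap is 5 to 6 percentage points in control discontinuation, too large for rounding. It is a wrong figure in the text, not a detail that could be left to an analysis plan.

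The consequence depends on which input is meant. If 45%, the stated 13 points and 80% power stand. If 2.5% per month, the difference is about 11 points and power at N = 458 about 69%. Both results rest on a two-sided 5% test, 6% dropout and an overall relative risk of 0.72. The first and last of these are inferred because they reproduce the stated 458 and 32%; the document does not state them.

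**What to change.** State which control input is intended and make the rate, the 20-month risk, the difference and the power agree. Either:

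1. keep 45% and correct the monthly rate to about 2.9% to 3.0%, with its support, in which case 80% power for 13 points stands; or
2. keep 2.5% per month and restate 20-month retention as about 60% versus 71%, an 11-point difference, with about 69% power at N = 458, adding that 80% power holds only for a difference of about 12.6 points.

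In either case, state the alpha and its sidedness, and say that 0.6 applies to the 70% expected to adopt, giving 0.72 overall.

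The cost is one reworded paragraph. N, endpoint, allocation and analysis do not change. Under the second option the stated power becomes less favourable. Enrollment was still under way at publication, so the correction is best recorded before the primary analysis.

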## Results

### Overview

The HOT4PrEP trial is a hybrid implementation study that randomizes new or current HIV PrEP patients at the Sexual Health Clinic in Seattle, Washington, to have the option of home-based monitoring with self-collection of samples for HIV, syphilis, gonorrhea, chlamydia and creatinine and telehealth follow-up versus standard care including in-clinic visits and monitoring. The primary outcome is PrEP retention at 20 months.

Enrollment for the trial began in March 2022 and continued through May 2022 when all research was halted in the SHC to focus on the emerging mpox outbreak. Study enrollment then resumed in December 2022 and is ongoing.

From March 2022 to May 2023, a total of 161 PrEP patients were screened to enroll the first 100 participants into the intervention arm (49/100, 49%) or standard care arm (51/100, 51%). In total, 2 PrEP patients (1.2%) were deemed ineligible to enroll, 55 (34%) declined to participate, and staff were not able to discuss enrollment with 4 (2.5%) patients. Common reasons for declining to participate included preferring to come into the clinic or having an aversion to seeing blood during the self-collection process.

Table 1 describes demographics and other baseline characteristics participants self-reported upon enrollment. The baseline survey completion rate was 96% for both trial arms. Median age was 34 (IQR 28-39, range 19-67) years. Of the participants who elected to provide sex and gender information, all were assigned male sex at birth (47/47, 100%). Most identified as cisgender men (41/47, 87%), gay (42/47, 89%), and their race and ethnicity as non-Hispanic White (n=36, 38%) or Asian (n=23, 24%). Most participants reported an annual income of US $30,000 or more (75%) and at least some college education (91%).

All participants in the intervention arm were contacted before their 4-month follow-up visit to ask if they would prefer to come into clinic or receive home kits. Of the 49 participants contacted, 33 (67%) opted to collect samples at home and follow up through telehealth, 14 (29%) opted to come in person to the clinic, and 2 (4%) canceled their appointments. Of those who opted for home sample collection and telehealth follow up, 27 (82%) returned test kits with samples for HIV and STI testing, 5 (15%) came in person to the clinic for their visit, and 1 (3%) canceled their appointment.

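### The relative risk of 0.6 is stated for everyone assigned to HB-PrEP, but the 32% discontinuation and N = 458 follow only if it applies to the 70% who adopt, which makes it 0.72 among those assigned

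*Protocol article*

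**What the plan says.** All the design inputs stand in the protocol article under Sample Size and Power Considerations. For the control arm, "we expect 45% of SOC participants to discontinue PrEP (55% retention) over the 20-month study period". For the intervention arm, "we estimate that 70% will adopt HB-PrEP". The next sentence gives the effect: "We assume a relative risk of discontinuation of 0.6 among participants assigned to receive HB-PrEP leading to a 32% discontinuation rate (68% retention". Dropout follows: "We also allowed for an overall dropout rate in both groups of 6"% (the percent sign completes the figure). The conclusion is that "a sample size of 458 participants should yield 80% power to detect a 13% point difference in PrEP retention", with 229 per arm. The method is described only in general terms: "Sample size calculations for the primary Kaplan-Meier survival analysis were based on standard methods". Alpha and sidedness are not given, and the section does not say what counts as adopting.

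Two other places bear on the point. Secondary Outcome Measures defines reach by use: the share of the HB-PrEP arm who send in home-collected specimens for at least half of their four-monthly visits. Results, Overview reports early uptake. Of 49 intervention participants contacted before the month 4 visit, 33 (67%) opted for home collection. Of those 33, "27 (82%) returned test kits with samples for HIV and STI testing", 5 came to the clinic and 1 cancelled.

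**The concern.** The effect sentence names the assigned population, while the figure it is said to produce belongs to a model in which only some of that population benefits. The two relative risks are far apart: 0.6 in those who use home monitoring, 0.72 in the arm as randomized. Primary Outcome Measures compares the arms, so 0.72 is the effect the trial is sized to detect. A reader who takes the sentence literally has the wrong benchmark for the primary result and cannot see that the 80% claim contains a 30% dilution.

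Once the dilution is visible, adoption becomes a design input in its own right, on a level with the control rate. The article prints early uptake data without linking them to that input. If the final comparison is null, the report will need to separate low uptake from lack of effect in users, and the stated design should make that possible.

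**Working it through.** **Inputs.** Control discontinuation 45%, adoption 70%, relative risk 0.6, intervention discontinuation 32%, dropout 6%, N = 458 (Sample Size and Power Considerations). 458 × 0.94 ≈ 430 evaluable, or 215 per arm. Assumed because not stated: two-sided alpha 0.05.

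**1. Reproduce the plan's N and power from 45% versus 32%.**
- Two proportions, unpooled variance: 432 in total; 432 / 0.94 = 460.
- Two proportions, pooled variance: 219 per arm, 438 in total; 438 / 0.94 = 466.
- Log-rank, Schoenfeld: HR = ln(0.68) / ln(0.55) = 0.645, 164 events; 164 / 0.385 / 0.94 ≈ 453 (0.385 is the mean of 0.45 and 0.32).
- Log-rank, Freedman: 169 events, about 467.

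All lie within 3% of 458. Power with 215 per arm is 79.3% (pooled proportions), 79.3% (Freedman) and 80.5% (Schoenfeld). The printed N and 80% belong to 32%.

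**2. Which reading of 0.6 gives 32%?**
- Relative risk 0.6 in everyone assigned: 0.6 × 0.45 = 27.0%.
- Hazard ratio 0.6 in everyone assigned: 1 − 0.55^0.6 = 30.1%.
- Hazard ratio 0.6 in the 70% who adopt, none in the rest: 0.7 × 30.1% + 0.3 × 45% = 34.6%.
- Relative risk 0.6 in the 70% who adopt, 1.0 in the rest: 0.45 × (0.7 × 0.6 + 0.3 × 1.0) = 0.45 × 0.72 = 32.4%.

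Only the last rounds to 32%, and its difference of 12.6 points rounds to 13. The gap between 27% and 32% is not rounding. At 27%, power with 215 per arm would be about 97–98%, and 80% power would need only about 237 people in total (111 per arm, 222 / 0.94).

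**3. Power as a function of adoption *a*.** Keep the plan's own model, 45% control and relative risk 0.6 in adopters, so that intervention discontinuation is 0.45 × (1 − 0.4*a*). For the pooled two-proportion test with n per arm, power = Φ{[d√n − 1.96√(2p̄(1 − p̄))] / √(p₁(1 − p₁) + p₂(1 − p₂))}, where p₁ and p₂ are the two discontinuation rates, d is their difference and p̄ their mean. For Schoenfeld, power = Φ(½√D·|ln HR| − 1.96), where D is the number of events. With 215 per arm, across the two-proportion, Freedman and Schoenfeld methods:

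| Adoption | Relative risk among those assigned | Discontinuation | Difference | Power |
|---|---|---|---|---|
| 70% (planned) | 0.72 | 32.4% | 12.6 points | about 77–78% |
| 33/49 = 67% (opted in) | 0.73 | 32.9% | 12.1 points | about 73–75% |
| 27/49 = 55% (returned a kit) | 0.78 | 35.1% | 9.9 points | about 55–57% |

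**4. Uncertainty of the last row.** The 95% Wilson interval for 27/49 is 41% to 68%. Power at those limits is about 34–35% and 74–75%.

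**The case against.** The strongest reply is that little turns on the wording. The same paragraph prints the arm-level target (32%, 68% retention), the 70% adoption and the 13-point difference, so a careful reader can recover the design effect. N and the planned comparison are untouched. This stands as a limit on the harm. It does not remove the error: the sentence names a population for which its own arithmetic fails. The word cannot simply be read as meaning users either, because the definition of reach separates being assigned to the arm from sending in specimens.

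The second reply concerns the adoption figures, and most of it stands. A reader might infer from the early data that the trial has only 56% power. The documents do not support that as an unconditional statement:
- The 55% comes from 49 people at one visit, and Home Specimen Tracking offers kits again at months 8 and 16, so use may rise or fall.
- The intervention is the option of home monitoring. Zero benefit for the 6 who opted in without returning a kit is an assumption, and 5 of those 6 attended the clinic.
- The section leaves adoption undefined. On the opt-in reading, 67% (95% interval 53–79%) is compatible with the planned 70%.
- Principal Findings in the Discussion already warns that stated preference may not turn into consistent use.

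A reader might also notice that 2.5% per month does not compound to 45% over 20 months and lower the power further on that account. That is a separate inconsistency. The documents do not settle which of the two figures is wrong, so 45%, on which N was built, is kept throughout.

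**Conclusion.** The stated population for the relative risk of 0.6 is wrong. As written it implies 27% discontinuation; the stated 32% and N = 458 require 0.6 among adopters and 0.72 among those assigned. This part needs no outside assumption. A reader might conclude that the sample size itself was miscalculated. It was not: 458 agrees with 45% versus 32% under standard methods if two-sided alpha is 0.05.

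Two smaller conclusions follow under that same alpha. Carrying 32.4% unrounded puts power at about 77–78% after dropout, so rounding accounts for two to three points of the claimed 80%. And the claim is sensitive to adoption: the values below the planned 70% are conditional sensitivity figures that assume no effect in non-users and let first-visit behaviour stand for adoption over 20 months. They show what the claim depends on. They do not estimate the trial's actual power.

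**What to change.** Restate the assumption along these lines: relative risk of discontinuation 0.6 among adopters; with 70% adoption, 0.72 among those assigned (32.4% discontinuation, a 12.6-point difference, about 77–78% power with 215 per arm), giving the alpha and sidedness used.

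Say what adoption means in the power calculation by pointing to the use-based reach definition in Secondary Outcome Measures; do not add a second definition. First-visit kit return is not itself reach, which is judged over the study period, so the early figure should be labelled as provisional.

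Beside the 80% claim, add a short sensitivity statement giving power at 70%, 67% and 55% adoption, with the 41–68% interval, the resulting power range of about 34–75%, and the assumption of no benefit without kit use.

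The cost is wording only. One printed power figure becomes slightly less favourable; N, randomization and the primary analysis do not change.
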